## Abstract

**Background:**

Chronic illnesses can have an unfavorable impact on the participation opportunities of children and adolescents. The German health care system offers medical rehabilitation in order to prevent negative effects, however, migrant children and adolescents make use of this option less frequently than their peers without a migrant background. A multimodal information campaign was developed to increase the use of medical rehabilitation by children and adolescents with a migrant background, and to reduce disparities in health care.

**Methods:**

The process evaluation will examine the implementation of a multimodal information campaign intended to increase the use of medical rehabilitation by migrant children and adolescents. The information campaign follows a low-threshold participatory approach. In a first step, persons from different migrant communities in Berlin and Hamburg are trained to become transcultural health mediators. These mediators then share their knowledge about chronic illnesses and medical rehabilitation with other families at information events held in their native language. The transcultural mediators also support migrant families in applying for medical rehabilitation. The effectiveness of the intervention will be tested by a trend study with repeated cross-sectional surveys. For this purpose, all families in the project regions of Berlin and Hamburg whose child has received medical rehabilitation are surveyed annually in order to be able to map changes in the proportions of children and adolescents with a migrant background over the course of the project.

**Discussion:**

The study protocol describes a complex intervention to increase the use of medical rehabilitation by migrant children and adolescents, and the accompanying process evaluation and trend study. The intervention is intended to contribute to reducing health inequalities in Germany.

**Conclusion:**

The study described in this protocol will provide extensive data on the multimodal information campaign and can thus help organizations and institutions adapt or further develop similar measures for other regions.

**Clinical trial registration:**

German Clinical Trials Register (DRKS00019090).

## Introduction

1.

Worldwide, the number of international migrants has grown significantly over the past 50 years. While in 1970 about 84 million people, or 2.3% of the world’s population at that time, lived in a country other than the one of their birth, in 2020 there were about 280 million people, or 3.6% of the world’s population (1). The reasons for migration movements are complex. In addition to civil unrest, war events, and natural disasters, economic and political conditions can be a major factor. Migration movements raise different challenges for countries of origin as well as destination countries. For example, while origin countries struggle with a loss of knowledge and skills, destination countries are required to create conditions that enable inclusion and inclusive transformation of structures in the different sectors of the social system. This includes the domain of health care, which must respond to citizens with different biographical experiences and resulting expectations and needs. In this paper, we describe a multimodal information campaign and associated evaluation that is designed to improve health care for migrant children in Germany.

### Germany as a country of immigration

1.1.

German society today is characterized by a variety of different ethnic, cultural and social backgrounds of its citizens. There have been various waves of migration since the foundation of the Federal Republic of Germany and the German Democratic Republic in 1949. In the first years after the end of World War II, it was mainly people from the former eastern territories (i.e., territories of today’s Poland and Russia) who moved to the Federal Republic of Germany, and they were followed in the 1950s by migrant workers from countries such as Italy, Spain, Greece, Turkey and Portugal. In addition to a steady influx of late re-settlers from states of the former Soviet Union, people fleeing their countries due to wars and civil wars (e.g., the Bosnian War of 1992–1995) found a new home in Germany. Although numerically inferior to migration to Western Germany, the German Democratic Republic also experienced the arrival of migrant workers from countries, such as Vietnam, Mozambique and Cuba. More recently, free movement for citizens of EU member states, which has been guaranteed by the European Union since 1993, has made it easier for people with diverse migration biographies to live in Germany. According to OECD data, Germany is nowadays the most common immigration destination after the USA (2). In 2019, around 26% of the total population in Germany had a migrant background (MB), i.e., their own or family migration history. In the under-18 age group, the proportion was around 39% (3).

### Migrant health in Germany

1.2.

Although the individual circumstances of children and adolescents with a MB can vary widely depending on family history, surveys show that children and adolescents with MB tend to be socioeconomically disadvantaged, and, for example, have a higher risk of poverty than their peers without a MB (4). Lower socioeconomic status is also associated with more frequent health problems and health-related risks in children and adolescents, as it is in adults (5, 6). This also applies to chronic diseases (e.g., obesity, attention deficit hyperactivity disorder), which are of particular importance because they can permanently jeopardize age-appropriate development and restrict the social participation of children and adolescents in the long term (7, 8). Chronic illnesses in children can also lead to psychosocial stress for close relatives such as parents and siblings (9, 10). Epidemiological studies estimate the proportion of chronically ill children in Germany to be about 16.2% (11). A migrant background in Germany is not a risk factor for a chronic disease in children and adolescents *per se*, however, there is a clear correlation between socioeconomic status and various disease patterns, such as obesity or mental disorders, which is why children and adolescents with MB are also more frequently affected by some diseases due to their comparatively low socioeconomic status (12).

### Medical rehabilitation for children and adolescents

1.3.

In general, children with chronic diseases in Germany are treated on an outpatient basis close to home by pediatricians or family doctors, in collaboration with other therapists (e.g., physiotherapists, child and adolescent psychotherapists). Outpatient treatment, however, may be not sufficient for some individuals. In these cases, the German social insurance system offers medical rehabilitation for children and adolescents (MRCA) (13). The legal basis for this is § 15a SGB VI. MRCA is intended to counteract the consequences of chronic illness, to enable schooling and vocational training without restrictions, and, in the long term, to prevent endangerment to, or the restriction of, gainful employment. In Germany, statutory health insurance and German Pension Insurance (GPI) are in principle equally responsible for medical rehabilitation. Despite this, the primary provider of MRCA services is the GPI. Every year, more than 32,000 requests for medical rehabilitation for children and adolescents are submitted to the German Pension Insurance. In Germany, medical rehabilitation for children and adolescents takes place almost exclusively in inpatient rehabilitation clinics. The most common reasons for using MRCA in 2018 were mental and behavioral disorders, followed by bronchial asthma, obesity and skin diseases such as neurodermatitis (14). Reliable data on the utilization of medical rehabilitation by children and adolescents with MB is not currently available, as the GPI administratively only records the nationality of rehabilitants. In terms of nationality, however, there is a clear underrepresentation of children and adolescents of non-German nationality (14). A recent study with adults shows that in addition to underutilization among persons without German nationality, underutilization by persons with a migration history can also be assumed (15). Possible reasons for this are utilization barriers such as insufficient language skills, a different understanding of illness, or insufficient knowledge of the German health care system (16).

### Promoting change

1.4.

The current care situation of children and adolescents with MB has encouraged the development and implementation of a complex intervention to increase the use of medical rehabilitation by children and adolescents with MB. We hypothesized that an increase in utilization could be achieved by increasing awareness of chronic conditions and the options for medical rehabilitation by offering low-threshold proactive information. Although there is already a variety of information on medical rehabilitation for children and adolescents, it is often only available in German. Moreover, there is also a question regarding the extent to which the current dissemination channels (e.g., via websites and counseling centers of official institutions) are suitable for reaching migrants in Germany. As the World Health Organization (WHO) has pointed out, the inclusion of migrants or migrant communities in the provision of information can be a suitable means of successful health promotion (17). Our project “Implementation and evaluation of a multilingual information campaign on rehabilitation for children and adolescents with a migrant background (MiMi-Reha-Kids)” follows this approach, in which migrants are actively involved in health education within the framework of a multimodal information campaign, and knowledge is consolidated in the migrant communities. The aim of the accompanying process evaluation and trend study is to clarify whether the information campaign increases access to and utilization of medical rehabilitation among children and adolescents with a migrant background.

## Methods

2.

### Setting

2.1.

The intervention to increase the use of medical rehabilitation by children and adolescents with a migrant background is based on previous campaigns of the Ethno-Medical Center e. V. (EMC) (18, 19). The assumption that migrants in health care provision should not only be seen as the target of advice and support, but as central actors in their own social and health-related integration with genuine resources and competencies is central to the project. The project is funded by German Pension Insurance Berlin-Brandenburg (GPI BB) and German Pension Insurance North (GPI North). The intervention consists of four modules: 1. mediator training (Module 1), 2. information events (Module 2), 3. individual support for rehabilitation requests (Module 3), and 4. transcultural training for health professionals (Module 4). The individual modules are described in detail below. The implementation takes place in the two cities of Berlin and Hamburg. These cities were chosen because they have a particularly high proportion of people with a migrant background (Figure 1), and a high population density due to their urban structure, which facilitates the feasibility of the individual modules within the framework of the limited financial and human resources in the trial (3).

**Figure 1 fig1:**
[figure not shown]
Proportion of the population with a migrant background in the 0 to 17 age group by federal state in Germany in 2019; Own representation based on data from the Federal Statistical Office (3).

The implementation is accompanied by a process evaluation (20). The effect of the intervention (i.e., increase in utilization of MRCA by children and adolescents with a migrant background) will be tested with a repeated cross-sectional survey (trend study) with four measurement points. The information campaign will be implemented by the Ethno-Medical Center. The process evaluation and the trend study are both implemented by the Institute of Social Medicine and Epidemiology of the University of Lübeck (UoL). The implementation of the information campaign, the implementation of the trend study and the process evaluation are accompanied by an advisory board, which consists of responsible persons from the GPI BB and GPI North sponsors as well as migration experts and specialists from the fields of pediatric and adolescent medicine and medical rehabilitation. The advisory board meets every six months and uses its expertise to address problems that arise during the implementation. The project started in April 2019, and once the campaign module design and materials development were completed, the campaign modules began implementation in September 2020. Implementation of the campaign modules and process evaluation will continue to the end of 2022. The final survey of the trend study will take place at the end of 2023.

### The intervention and underlying assumption

2.2.

Health promotion interventions tailored to the needs of subgroups or communities within an overall population may be better suited to addressing health inequalities within a population (21, 22). Accordingly, the WHO also recommends the greater involvement of migrants and migrant communities in health promotion interventions in order to strengthen their personal health literacy and reduce inequalities (17). The intervention described here follows these principles. The intervention builds on the EMC’s concept “MiMi – With Migrants, For Migrants” (18, 19). The concept follows a setting approach, which sees the consideration and inclusion of the social environment as a central aspect of successful measures to improve health behavior (23). In the context of MiMi-Reha-Kids, this means taking appropriate account of the heterogeneous social environment of migrants in Germany, and actively involving migrants in the process of health promotion. In order to ensure this, MiMi-Reha-Kids follows an empowerment strategy by training people from migrant communities to become transcultural mediators, who then act as multipliers in their communities, conducting information events in their native language and supporting families in requesting medical rehabilitation for children and adolescents.

Migrants are thus actively involved in local health promotion, and knowledge is anchored in migrant communities. Information can be passed on according to the specific needs of people with MB, since the members of the communities can be seen as experts for their own social environment, and therefore know best who can be addressed where, when and how in a target group-oriented manner, and informed about the topic of medical rehabilitation for children and adolescents. Together with external instructors, the project managers conduct the initial training sessions and develop multilingual materials. These materials will be used by the mediators to conduct the information events and support rehabilitation requests. Further training on transcultural competence is also offered for health care professionals in order to raise awareness about the specific needs of families with migrant backgrounds. During the initial phase of intervention development, qualitative interviews will be conducted with parents with a history of migration and a chronically ill child, as well as chronically ill adolescents themselves, in order to identify additional barriers and challenges in accessing medical rehabilitation and to tailor the modules of the information campaign accordingly. Additional file 1 describes the four modules according to the Template for Intervention Description and Replication (TIDieR) (24).

#### Mediator training (Module 1)

2.2.1.

The intervention starts with the acquisition of future transcultural mediators from different migrant communities (e.g., Turkish community) at the project sites in Berlin and Hamburg. Contact and acquisition is through the EMC network, and considers the social environment of the migrants. Potential mediators are recruited, for example, in religious, social, and migrant self-organizations, cultural centers or in educational institutions using flyers, posters, or by word of mouth. The recruitment targets individuals with advanced German skills and extended networks in the respective migrant community. The mediators are provided with knowledge about the general and health situation of migrant families in Germany, and about the German health care system, in extensive training courses (Module 1), with a special focus on medical rehabilitation, its goals, contents and possible uses. The mediators are also taught didactic and methodological skills in the training sessions, which enable them to pass on their acquired knowledge to other members of the migrant communities as multipliers in independently organized information events. The entire training comprises 48 teaching units of 45 min each, which are distributed over nine training days. The sessions are led by instructors with subject-specific experience (e.g., pediatricians on the topic of chronic diseases in children). Participants receive a training folder with prepared information on the training content. On the last day of training, the trained mediators give a presentation in small groups on one of the topics covered in the training (e.g., requesting on medical rehabilitation for children and adolescents) as a final exam. A total of at least 120 mediators (60 in Berlin and 60 in Hamburg) will thus be trained in three years from 2020 to 2022.

#### Information events in the native language (Module 2)

2.2.2.

After completing the training, the mediators inform migrants about medical rehabilitation for children and adolescents in independently conducted information events in their native language (Module 2). In addition to their training folder, the trained mediators receive other support materials, such as a multilingual guide to medical rehabilitation for children and adolescents (see Additional file 2) that can be handed out to interested parents and adolescents, and a PowerPoint presentation that they can use for the information session. Both the guide and the presentation present the contents of the training in a condensed and easy-to-understand form. In addition to a German-language version, these materials are available in Arabic, Bulgarian, English, Farsi, Italian, Kurdish, Polish, Russian, Spanish, Serbian/Croatian/Bosnian and Turkish, so that information events can be held in the native language of parents and interested parties. The information events should have a duration of about 120 min, and be carried out with about 10 participants. The information events can take place at different locations in the migrants’ social environment, for example in migrant cultural associations, but also in doctors’ offices, schools or EMC venues. The mediators are responsible for organizing the sessions themselves, but receive support from the EMC if necessary. The mediators receive a financial compensation for each information session held. Overall, it is planned that the mediators will hold a total of 240 information events by the end of 2022, thus informing around 2,400 people in Berlin and Hamburg about the possibilities of medical rehabilitation.

#### Individual support for rehabilitation requests (Module 3)

2.2.3.

In addition to information events, the trained mediators offer individual support for rehabilitation requests (Module 3). Families with chronically ill children can receive advice in their native language on the process for requesting medical rehabilitation or filling out the application forms with the support of the mediators. The mediators can use a written guide on how to apply for medical rehabilitation for children and adolescents, which was designed within the project. The counseling can take place in a public location, at the home of interested persons, or in venues of the EMC. The counseling service is also particularly important because application forms for medical rehabilitation in Germany are currently only available in German. The mediators receive financial compensation for each consultation on a rehabilitation request. A total of 48 individual consultations are to be carried out by the mediators.

#### Transcultural training for professionals (Module 4)

2.2.4.

Transcultural competence, i.e., culture-related knowledge, sensitivity toward different life worlds and the ability to critically reflect on one’s own sociocultural location (25), is a key-competence in achieving better outcomes in health-related interaction and communication among individuals with different sociocultural backgrounds (26). The project therefore also aims to promote the transcultural competence of health professionals. A total of at least four all-day training courses on transcultural competence and communication (Module 4) will be held in 2021 and 2022 in Berlin and Hamburg for health professionals from the field of rehabilitative care who are either directly involved in the implementation of medical rehabilitation (e.g., therapists and nurses from rehabilitation centers), or have a steering function in the process of medical rehabilitation for children and adolescents (e.g., pediatricians). The training sessions are offered by external certified coaches for transcultural communication. By raising awareness on barriers specific to the project target group (e.g., language-and culture-based barriers), the trainings strengthen the integrative competence of health professionals when counseling and treating persons from migrant backgrounds. There is no fee to attend.

### Evaluation design

2.3.

In order to evaluate the intervention, we combine a trend study consisting of a repeated retrospective cross-sectional survey (27) at four measurement time points (2020, 2021, 2022, 2023), with an accompanying process evaluation of the information campaign. The process evaluation is based on the recommendations of the British Medical Research Council for complex interventions (20). The evaluation of complex interventions faces the challenge that when outcomes are being assessed it is not always immediately determinable which elements have contributed to success or non-success in the sense of describable effects on the outcome, due to the multiplicity of different elements and their possible interactions (28). A description of the assumed mechanism of action of the intervention together with an evaluation of the implementation of the individual intervention elements (e.g., reach, dose delivered, dose received), can help to better understand which factors of the complex intervention may have affected the outcome (28). Knowledge about implementing the different modules is not only important to explain observed outcomes, however, but also with regard to the further development or adaptation of the intervention in other settings. The potential mechanism of impact for the MiMi-Reha-Kids intervention and the interaction of the different modules is shown in Figure 2.

**Figure 2 fig2:**
[figure not shown]
Potential mechanism of impact for the Multilingual Information Campaign on Rehabilitation for Children and Adolescents with Migrant Background.

As part of the process evaluation, questionnaires will be used to continually collect data on the implementation of the individual modules of the intervention during the active implementation of the information campaign from October 2020 to December 2022. The data collected describes, for the different modules mentioned above, and among other things, the scope of the sessions (duration, frequency), the number of participants, the socio-demographics of the participants, implemented content, the subjective assessment of the information gain, and challenges of implementation. Data will be collected from both participants and instructors (Table 1). The effectiveness of the intervention will be tested by a trend study with repeated retrospective written cross-sectional surveys in the project sites of Berlin and Hamburg of families in which a child lives who received medical rehabilitation from German Pension Insurance in the previous year, in order to describe the change in the proportion of rehabilitants with a migrant background. The first cross-sectional survey was conducted in the fourth quarter of 2020, and is used to describe the proportion of children and adolescents with a migrant background in 2019 and thus before the implementation of the information campaign. The last retrospective cross-sectional survey will take place in the fourth quarter of 2023. The questionnaire data will be linked to the administrative data of the applicants.

**Table 1 tab1:** Description of the process evaluation tools and elements.

Module	Process evaluation tool	Process evaluation element	Information/Data
Mediator training (Module 1)			
	Recruitment monitoring	Recruitment/reach	Number of mediators per training
	Documentation sheet for instructors	Recruitment/reach	Number of mediators per training unit
		Fidelity	Implementation of the module in comparison to the conceptual design (e.g., duration, contents); Feedback from instructors on implementation problems with closed and open-ended questions
		Dose delivered	Duration of the training course
			Materials used
			Subjective evaluation of the training course implementation from the instructor’s point of view
	Questionnaire 1 for mediators (at each individual appointment)	Dose received	Subjective evaluation of the implementation of the training date
			Recommendations of the mediators to improve training
	Questionnaire 2 for mediators (after completion)	Recruitment/reach	Sociodemographic data of the mediators
		Dose delivered	Data on attendance at the individual training dates
		Dose received	Subjective evaluation of the implementation of the entire training
			Recommendations of the mediators to improve training
Information events in the native language (Module 2)			
	Documentation sheet for mediators	Recruitment/reach	Number of participants
		Fidelity	Implementation of the module in comparison to the conceptual design (e.g., duration, contents); Feedback from mediators on implementation problems with closed and open-ended questions
		Dose delivered	Location of the information session
			Duration of the information session
			Information session language
			Sociodemographic data on the mediator performing the mediation
			Materials used
			Information on topics covered
			Subjective evaluation of implementation of the information session from the mediator’s point of view
	Questionnaire for participants in twelve languages	Recruitment/reach	Sociodemographic data of the participants
		Dose received	Subjective evaluation of implementation of the information session
Individual support for rehabilitation requests (Module 3)			
	Monitoring of the implementation	Dose delivered	Number and duration of consultations
		Recruitment/reach	Number of participants, language of consultations
	Documentation sheet for mediators	Fidelity	Implementation of the module in comparison to the conceptual design (e.g., duration, contents); Feedback on implementation problems with closed and open-ended questions
Transcultural training for professionals (Module 4)			
	Recruitment monitoring	Recruitment/reach	Number of participants
	Documentation sheet for instructors	Fidelity	Implementation of the module in comparison to the conceptual design (e.g., duration, contents); Feedback from instructors on implementation problems with closed and open-ended questions
		Dose delivered	Training duration
			Subjective evaluation of implementation of the training from the instructor’s point of view
	Questionnaire for participants of the training	Recruitment/reach	Sociodemographic data of the participants
		Dose received	Subjective evaluation of implementation of the training from the point of view of the participants

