#### Trend study

2.4.1.

The sample for the repeated cross-sectional survey of the trend study consists of all insured persons with the Federal German Pension Insurance, German Pension Insurance Berlin-Brandenburg, and German Pension Insurance North residing in Berlin or Hamburg whose child received medical rehabilitation through the German Pension Insurance in 2019, 2020, 2021, or 2022 and were aged from 0 to 17 years at the time of utilization. These three providers collectively account for the majority of the insured population in the two model regions, making it possible to include nearly all eligible families in the sample.

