#### Trend study

2.5.1.

The primary outcome of the trend study on the utilization of rehabilitation is the proportion of children and adolescents with a migrant background among those undergoing rehabilitation who reside in Berlin or Hamburg. The migrant background is assessed in this study in accordance with the minimum indicator set for recording migration status (29).

We determine an individual as having a migrant background if they immigrated from another country and have at least one parent who was not born in Germany, or have two parents who immigrated and/or do not have German nationality.

This definition allows a differentiation between children with unilateral and bilateral migrant backgrounds (30). The information on the country of birth and nationality of the parents and the child required to map the migrant background is assessed through a questionnaire, and combined with data from the insured person’s account. The primary language, residence status, and duration of residence of the child and the child’s parents are also assessed.

In order to provide a description of the samples and to describe differences between children and adolescents with and without a migrant background in the samples, the health-related quality of life of the children and adolescents [KIDSCREEN-27 (31)], sociodemographic and socioeconomic information on the children and the parental home (32), perceived social support (33) and satisfaction with the rehabilitation service received will be collected through questionnaires as part of the trend study. The questionnaire data is supplemented by administrative data on medical rehabilitation (e.g., duration, and discharge diagnosis according to ICD-10) from parents’ insurance accounts. The data collected in the trend study is shown in Table 2.

**Table 2 tab2:** Data collected as part of the trend study.

Data	Source^2^	Sample 2020	Sample 2021	Sample 2022	Sample 2023
Migration history (34)		x	x	x	x
Nationality^1^	Questionnaire for parents/administrative data	x	x	x	x
Country of birth^1^	Questionnaire for parents	x	x	x	x
Primary language^1^	Questionnaire for parents	x	x	x	x
Duration of stay^1^	Questionnaire for parents	x	x	x	x
Residence status^1^	Questionnaire for parents	x	x	x	x
Socioeconomic status (31)	Questionnaire for parents	x	x	x	x
Social support (32)	Questionnaire for parents	x	x	x	x
Health-related quality of life (KIDSCREEN-27) (30)		x	x	x	x
Physical wellbeing	Questionnaire for parents/child	x	x	x	x

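### The trend test is presented as a test of campaign effectiveness, but without a comparison area it can only show that the migrant share changed in the two campaign cities.

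*Protocol article*

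**What the plan says.** The aim is causal. Section 1.4 says the evaluation is to clarify "whether the information campaign increases access to and utilization of medical rehabilitation among children and adolescents with a migrant background". Section 2.3 says "The effectiveness of the intervention will be tested by a trend study with repeated retrospective written cross-sectional surveys in the project sites". The Abstract, section 2.1 and the Discussion also speak of testing the effect or effectiveness of the intervention.

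The design is confined to the campaign cities:

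- **Sample** (section 2.4.1): insured persons of three carriers "residing in Berlin or Hamburg whose child received medical rehabilitation through the German Pension Insurance in 2019, 2020, 2021, or 2022".
- **Primary outcome** (section 2.5.1): "the proportion of children and adolescents with a migrant background among those undergoing rehabilitation who reside in Berlin or Hamburg".
- **Analysis** (section 2.10): a Cochran-Armitage test for trend, two-sided at 0.05, with no comparison term.
- **Baseline** (section 2.3): the first survey "is used to describe the proportion of children and adolescents with a migrant background in 2019 and thus before the implementation of the information campaign". Section 2.1 dates the start of the campaign modules to September 2020, so 2019 is the only rehabilitation year wholly before any module, and 2020 is mixed.

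Section 1.3 says that the pension insurance records rehabilitants' nationality but not migrant background, and reports from nationality that "In terms of nationality, however, there is a clear underrepresentation of children and adolescents of non-German nationality".

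**The concern.** The trend test asks whether the migrant share stayed constant over 2019 to 2022. The study asks whether the campaign raised use. The two coincide only if the share would have stayed constant without the campaign. Nothing in the design checks that: there is no area without the campaign, and one clean earlier year cannot show a prior trend.

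Several ordinary changes could move the share, such as growth of the migrant child population or a change in carrier policy. The outcome is a proportion among rehabilitants, so it also rises if fewer children without a migrant background take up rehabilitation while migrant use stays the same.

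At stake is the main conclusion. A significant rise could be published as evidence that the campaign works, and used to extend it to other regions, when the 5% error rate applies only to the narrower question of constancy.

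**Working it through.** **Inputs.** From section 2.6.1: planned shares 10, 11, 13 and 16%; 432 persons per year; 40% participation of 1,200 children, read as 480 per year; power 84%. From section 2.10: two-sided 0.05.

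**Formula.** With equal n per year and centred scores d = −1.5, −0.5, 0.5, 1.5 (Σd² = 5):

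- T = n·Σd·p
- SE0 = √(n·p̄(1−p̄)·5), with p̄ the mean share
- SE1 = √(n·Σd²·p(1−p))
- P(significant increase) = Φ((T − 1.96·SE0)/SE1)

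**The plan's own figure.** Σd·p = −0.150 − 0.055 + 0.065 + 0.240 = 0.10 and p̄ = 0.125.

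- n = 480: T = 48.0, SE0 = 16.20, SE1 = 16.36; (48.0 − 31.76)/16.36 = 0.993, power 84.0%.
- n = 432: T = 43.2, SE0 = 15.37, SE1 = 15.52; 0.842, power 80.0%.

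The stated 84% is reproduced, and 432 is the smallest n that reaches 80%. The sample-size arithmetic is sound. The planned alternative has a weighted slope of 0.10/5 = 2 percentage points per year.

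**No campaign effect, assumed background drift.** Let p = 0.10 + b·t for t = 0 to 3. Then Σd·p = 5b, and at n = 480 T = 2400·b. The values of b are assumptions, as the article gives none.

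| Drift b (points/year) | T | SE0 | SE1 | z | Significant increase, n = 480 | n = 432 |
|---|---|---|---|---|---|---|
| 0 | 0 | 14.70 | 14.70 | −1.96 | 2.5% | 2.5% |
| 0.25 | 6.0 | 14.94 | 14.94 | −1.558 | 6.0% | 5.7% |
| 0.5 | 12.0 | 15.17 | 15.17 | −1.169 | 12.1% | 11.3% |
| 1 | 24.0 | 15.63 | 15.61 | −0.425 | 33.6% | 30.7% |
| 2 | 48.0 | 16.48 | 16.42 | 0.957 | 83.1% | 79.0% |

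Simulation (200,000 runs per case) agrees. For drifts of 0.5, 1 and 2 points its two-sided rates at n = 480 are 12.4%, 33.6% and 83.2%.

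**Denominator example (assumption).** Hold migrant rehabilitants constant and let the others fall by 10% a year: 48 against 432, 388.8, 349.9 and 314.9. The share goes 10.0, 11.0, 12.1, 13.2% with no change in migrant use. With n held at 480 for simplicity, Σd·p = 0.0538, T = 25.8 and z = −0.313, giving a significant increase in 38% of trials. The figure would be somewhat lower if respondent numbers fell too.

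**What a comparison could deliver.** Suppose the same outcome were measured in a comparison area that stays flat at 10%. The difference in trends is 0.10, with SE = √(0.5577/480 + 0.45/m).

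- m = 480: SE = 0.0458; 0.10/0.0458 − 1.96 = 0.22, power 59%.
- m = 4,800: SE = 0.0354; 0.10/0.0354 − 1.96 = 0.86, power 81%.

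A nationality comparison would involve other rates, which the article does not give, so its power cannot be computed.

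**The case against.** The uncontrolled design is stated openly, and section 2.1 gives limited resources as a reason for working in these two cities. The section 2.3 sentence goes on to speak of describing the change in the proportion, and the Conclusion speaks of use over the intervention period at the intervention sites. Part of the text is therefore already descriptive. This stands, but it makes the wording inconsistent and does not remove the causal aim in section 1.4 and the Discussion. The Conclusion also says changes can be related to how the modules were carried out. Process data show what was delivered, not what would have happened without it.

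The error rates rest on assumed drifts, and the 2-point case is nearly the planned power under another name. This also stands. Demographic drift alone may be small. Section 1.1 puts the migrant share of under-18s at about 39% in 2019. If that rose by an assumed 1 point a year and the 10% scaled with it, the drift would be 10% × 1/39 ≈ 0.26 points a year, giving a significant increase in about 6% of trials.

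A reader might infer that a comparison series is ready to use. Section 1.3 does not support that. It says nationality is recorded, but nothing about completeness, regional or pre-2019 series, or release. The only data route described (section 2.8.1) is individual and consent-based. Comparable trends are also doubtful, because section 2.1 says the cities were chosen for their particularly high migrant share.

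**Conclusion.** The point holds as a mismatch between claim and design. The planned test can show that the migrant share changed in Berlin and Hamburg. It cannot separate a campaign effect from background change.

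The size depends on a drift the article does not give. With none, a false increase appears in 2.5% of trials. With 0.25 to 1 point per year it appears in about 6% to 34% at n = 480. The 83% at 2 points per year is an upper illustration. These figures assume a 10% start, linear drift, equal n and no campaign effect.

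Two stronger readings are not supported. One is that any background change will produce a significant result: small drifts raise the rate only modestly. The other is that an effectiveness claim should stand or fall on a nationality interaction. Nationality is only a proxy, its power is unknown, and a campaign effect among migrant children with German nationality would be missed. The survey remains useful as a measure of change.

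**What to change.** 1. State that the survey trend test assesses change over time in the two cities and does not by itself establish campaign effectiveness. Align the Abstract (Methods), sections 1.4, 2.1 and 2.3, the Discussion and the Conclusion. This costs only editing.
2. Ask the participating carriers whether yearly aggregate counts of child rehabilitants by nationality can be supplied for Berlin and Hamburg and for areas without the campaign, including years before 2019. If they can, pre-specify a region-by-period comparison with a check of pre-campaign trends. Report it as a supporting analysis, not as a pass/fail condition.

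The second step costs one data request of unconfirmed feasibility. The two regional carriers fund the project and sit on its advisory board, so the channel exists. The surveys and the primary analysis stay as planned. The drawbacks are that nationality only approximates migrant background and that the interaction may have low power. If no extract can be had, the first step still stands.
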